### Outline of Confirmatory Designs

Psychological research is currently facing a substantial replication crisis (91), because its main focus lies on publishing spectacular positive findings instead of conducting methodologically sound replication studies (52, 92). As a result, many researchers involve in questionable research practices, meaning that data and statistical models are processed, transformed, and modified until one finds the desired association at *p* < 0.05 (93, 94). Such inadequate procedures, also referred to as *p*-hacking, often yield irreproducible, inflated, or false-positive associations (95–97). To avoid these systematic biases, various authors have called for more stringent confirmatory research designs (51, 98). To increase the objectivity and transparency of research designs, such an approach comprises that concise study and analysis protocols are published publicly online. These protocols not only define the exact study design, including sampling procedure, timing, and conduct of measurements, the applied assessment instruments, and the hypotheses to be tested but also which outcomes will be analyzed to test these predictions. To reduce the flexibility in analysis procedures, which markedly inflates the rate of false-positive findings (94), one therefore also prespecifies the exact statistical methods and how the outcome of interest will be modeled before the data are known. According to these state-of-the-art guidelines for confirmatory research (51, 98), we published the original study protocol submitted to the KEK publicly online using the Open Science Framework (https://osf.io/ukbs5/). The hypotheses related to the aims of this project stated in that document will be rephrased in more detail below.

### Instruments and Measures

Because this is a fully naturalistic study, we will use only instruments and measures that are routinely applied at the KGI to all patients. That is, to avoid methodological artifacts such as design or experimenter effects, we will not add additional assessment procedures that are not part of the basic psychotherapy evaluation. In consequence, the coverage and range of assessment instruments is limited those applied at the study site. However, note that there are further instruments applied at the KGI that are not considered in the present study, because they are administered only to selected patients with specific problems or because they were considered redundant for the present study aims. Normal-range personality will be assessed with a German adaptation (99) of the well-established Big Five Inventory (BFI) (100). The BFI is a brief self-report inventory capturing the basic structure of personality based on the broad domains of neuroticism, extraversion, openness, conscientiousness, and agreeableness. The BFI has been validated in diverse samples across nations, including English, German, Dutch, and Chinese, and is considered a reliable and valid short assessment of the FFM (99–102). Personality will be further assessed using the German adaptation (103) of the Inventory of Interpersonal Problems (IIP) (104). The IIP relies on the interpersonal circumplex model (105, 106) and captures personality difficulties based on the following eight primary domains of interpersonal problems, that is, domineering, vindictive, cold, socially avoidant, submissive, exploitable, overly nurturant, and intrusive. On a higher-order level, these domains collapse into the meta-factors of agency/dominance and communion/affiliation. The circumplex personality domains revealed strong and consistent associations with both the Big Five traits of extraversion and agreeableness and personality disorder dimensions (107–109), which is why personality pathology is considered a disorder of interpersonal behavior (110–112). In addition to the self-report IIP, an informant rating scale of the circumplex model will also be administered using the Impact Message Inventory-Circumplex (IMI-C) (113, 114). The informant rating will be provided by various sources; however, in most cases, the rater will be the partner/spouse or a family member. The BFI will be assessed at both baseline and 6-month follow-up, while IIP and IMI-C will be completed at baseline only due to their length.

Subjective psychopathological symptoms will be assessed with the German translation (115) of the Brief Symptom Inventory (BSI) (116). The BSI measures psychopathology based on the following nine syndromes: somatization, obsessive–compulsive, interpersonal sensitivity, depression, anxiety, hostility, phobia, paranoia, and psychoticism. Although these scales demonstrated good reliability (115, 116), due to rather poor convergent and discriminant validity, it has been suggested to use only the total impairment score (117). As an alternative measure of subjective impairment we will use the incongruence questionnaire (INK) (118). The INK measures motivational incongruence, defined as the discrepancy between a person’s motivational goals and his/her perception of the actual fulfilment of his/her socio-affective needs. The INK has shown good psychometric properties and correlates strongly with psychopathological distress, which makes it a valuable tool for treatment evaluation in psychotherapy research and practice (118, 119). Finally, the treating psychotherapist will quantify the global functioning of the patient using the Global Assessment of Functioning (GAF) scale (120) in order to obtain an objective other rating of his/her psychopathological impairment. All measures of psychopathology, that is, BSI, INK, and GAF will be administered both at baseline and 6-month follow-up. In addition to the inventories and rating scales detailed above, information from the patient chart, including diagnoses according to ICD-10, age, sex, and education level, will also be recorded in the dataset. The flowchart is shown in Figure 1.

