(1)BFI traits show high differential continuity over time (all *r* > 0.6). To test this prediction, we will compute bivariate Pearson correlations between trait scores at baseline and 6-month follow-up. We will provide both attenuated and disattenuated correlation coefficients corrected for scale unreliability.(2)BFI traits demonstrate substantial mean-level continuity (all *d* < 0.5). More specifically, we predict that only neuroticism will demonstrate modest mean-level change (0.2 < *d* > 0.5), while the other four traits will remain almost unaltered over time (all *d* < 0.2). These predictions will be tested with *t*-tests for paired samples by examining the differences in standardized mean-level change between baseline and 6-month follow-up.(3)Baseline BFI traits, specifically high neuroticism and low conscientiousness, substantially reduce (*d* > 0.5) the effectiveness of psychotherapy based on the BSI, GAF, and INK over the 6-month observation period. In order to test this prediction, we will compute GEE (121). These statistical models were introduced to fit regression analyses that account for within-subject correlation, which is an inherent part of longitudinal studies that rely on repeated outcome measures. Together with mixed models and random coefficient models, GEE represent the state of the art for longitudinal data analysis and are preferred to repeated measures ANOVA due to their superior psychometric properties (122, 123). The baseline BFI traits will be entered as the predictor variables and the repeated measures of the BSI, GAF, and INK successively as the outcome. The effect size of interest will be modeled as the interaction term between baseline personality and the time slope coefficient of the repeated outcomes, that is, the linear time trend for change in BSI, GAF, and INK. By simultaneously adjusting for the intercept, such a statistical modeling ensures that change in psychopathology over time is estimated independent of baseline impairment. These models will be conducted with and without adjustment for baseline diagnoses based on ICD-10.(4)Mean-level change in BFI traits is only weakly, if at all, correlated with change in psychopathological impairment over time (all *r* < 0.3). To test this hypothesis, we will compute individual change scores over time for all repeated measures by subtracting the baseline score from the follow-up score. The change scores of the BFI traits will then be correlated with the change scores of the BSI, GAF, and INK using Pearson correlation.

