
Second paper: the second confirmatory analysis will focus on the IIP and IMI-C. We will test the following hypotheses:
(1)Self-reports and informant ratings of interpersonal personality problems are only modestly correlated (all *r* < 0.3). To test this hypothesis, we will subject the IIP (self-report) and the IMI-C (informant rating) to a bivariate Pearson correlation analysis.(2)Both self-reported and informant-rated baseline personality problems according to the IIP and IMI-C substantially reduce (*d* > 0.5) the effectiveness of psychotherapy according to change in BSI, GAF, and INK from baseline to 6-month follow-up. As specified above with respect to the BFI, we will test these predictions by focusing on the interaction effect between baseline personality measures and the time slope coefficients of the psychopathology outcomes using a series of GEE analyses.(3)Self-other agreement in personality profiles relates stronger to the outcome of psychotherapy than either self-report (IIP) or informant rating (IMI-C). To test this hypothesis, we will first compute the index of profile agreement (*I*_pa_) between IIP and IMI-C as recommended by McCrae (124) and then compare the slope-interaction effect of the *I*_pa_ with the multivariable effects obtained for the IIP and the IMI-C domains based on the results of GEE as specified above. The difference between two effect sizes will be considered statistically significant if the 95% confidence intervals of their standardized regression coefficients do not overlap.(4)IIP and IMI-C have substantial incremental criterion validity (Δ*R*^2^ > 0.05) above and beyond each other in the prediction of the outcome of psychotherapy. This hypothesis will be tested by subjecting the change scores over time for BSI, GAF, and INK to a hierarchical linear regression analysis, where baseline IIP and IMI-C are entered in interchangeable hierarchical blocks as the predictor variables. In these models, the effect size of interest will be the amount of additional variance explained (Δ*R*^2^) accounted for by either IIP or IMI-C in the prediction of intraindividual change in BSI, GAF, and INK over time.

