### Caveats and Potential Pitfalls

We have stressed that clinical trials in psychotherapy and psychopharmacology commonly have poor external validity, that is, the efficacy of treatments for mental disorders as estimated in the laboratory under controlled conditions using selective samples only poorly corresponds to real-world effectiveness in unselected naturalistic samples (47, 48). On the other hand, clinical trials have considerably higher internal validity than observational studies, which is why they are considered the gold standard for the estimation of causal effects. That holds particularly true when the main objective is to evaluate the efficacy of a given intervention. Observational studies are merely correlational, as interventions cannot be randomly assigned to participants. Therefore, they do not allow for strict causal conclusions, although sophisticated statistical techniques such as propensity score matching can approximate the internal validity of observational designs to that of randomized experiments (125). However, as we are mainly interested in the longitudinal covariance between personality and psychopathology and in the stability of personality, but not on the efficacy of psychotherapy as an intervention *per se*, that potential limitation is not at issue. That is, we are not interested in testing the efficacy of an intervention, but rather in evaluating possible mechanisms operating within that particular intervention. We will therefore not apply propensity score matching, as we do not compare psychotherapy users with untreated patients or other treatment modalities. A bias that needs to be addressed in such a study is the content overlap between personality and psychopathology, in particular that between neuroticism and depression (126), as that bias might artificially inflate the association between these constructs. To solve that problem, we will apply outcomes such as the GAF and the INK that have no content overlap with neuroticism. Moreover, we will also use alternative measures of personality such as the circumplex model of personality problems, which will be assessed based on both self-report and informant rating. Finally, though we consider the heterogeneity of this representative sample a particular strength, one might also argue that we compare apples to oranges. That argument holds particularly true with respect to interindividual differences in baseline impairment. As detailed above, we will resolve that issue by applying statistical models that estimate the change in psychopathology over time while holding baseline impairment constant. In order to additionally control for distinct baseline psychopathology, we will also include a patient’s primary diagnosis as a covariate.

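### Age, sex and education are recorded, but diagnosis is the only covariate named for the GEE models, leaving adjusted trait-by-time effects open to demographic confounding

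*Protocol article*

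**What the plan says.** Under Instruments and Measures, the chart variables are listed: "diagnoses according to ICD-10, age, sex, and education level, will also be recorded in the dataset".

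Under Hypotheses and Planned Analyses, first paper, hypothesis (3), the target is a trait-by-time term: "The effect size of interest will be modeled as the interaction term between baseline personality and the time slope coefficient of the repeated outcomes". On covariates the article says: "These models will be conducted with and without adjustment for baseline diagnoses based on ICD-10". Baseline severity is handled through the model itself: "By simultaneously adjusting for the intercept, such a statistical modeling ensures that change in psychopathology over time is estimated independent of baseline impairment".

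The second paper takes over this specification for its hypothesis (2): "As specified above with respect to the BFI, we will test these predictions by focusing on the interaction effect". It names no further covariate. The hierarchical regressions of its hypothesis (4) enter only the IIP and the IMI-C.

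Caveats and Potential Pitfalls repeats the adjustment, now for one diagnosis per patient: "we will also include a patient’s primary diagnosis as a covariate". The same section concedes that "Observational studies are merely correlational, as interventions cannot be randomly assigned to participants". It then sets the matter aside because the interest lies in the covariance of personality and psychopathology, "but not on the efficacy of psychotherapy as an intervention *per se*, that potential limitation is not at issue".

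Age, sex and education appear in no stated hypothesis or model.

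**The concern.** The exposure here is the trait, and nobody is randomised to it. Patients range from 18 to 65 years. If older and younger patients, or men and women, improve at different rates and also differ in neuroticism or conscientiousness, part of that difference is credited to the trait.

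The article's reason for setting confounding aside is that no treatments are compared. That answers confounding of treatment. It does not answer confounding of the trait effect, which is what the models estimate. Adjusting for diagnosis and for starting level does not remove a demographic difference in rate of change either.

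The wording makes this matter. The hypotheses say that traits reduce the effectiveness of therapy, and the Caveats section says the study examines mechanisms within the intervention. Both go beyond prediction. The article also presents its analyses as exactly prespecified, so demographic terms added after the data are seen would be the analytic flexibility it warns against.

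**Working it through.** **Inputs from the article.** About 100 six-month follow-ups, alpha 0.05 (taken as two-sided), predicted trait effect d > 0.5, target the trait-by-time interaction. The figure n = 100 is a judgement from three sources, so no single formula reproduces it. It is compatible with a paired comparison at d = 0.3 (n = 90 for 80% power; power 0.844 at 100). It is not disputed here.

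**Assumed inputs.** One omitted covariate, with correlation 0.1, 0.2 or 0.3 with the trait and the same with change. True trait effect on change is zero.

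**Step 1: bias.** The spurious trait-change correlation is approximately r(trait, covariate) x r(covariate, change). As d this is 2r / sqrt(1 − r²). For comparison, d = 0.5 corresponds to r = 0.5 / sqrt(0.25 + 4) = 0.243.

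| Each correlation | Spurious r | As d | Share of 0.243 |
|---|---|---|---|
| 0.1 | 0.01 | 0.02 | 4% |
| 0.2 | 0.04 | 0.08 | 16% |
| 0.3 | 0.09 | 0.18 | 37% |

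The sign follows the product. If the two correlations have opposite signs, the bias is negative, so it can weaken a true effect as well as inflate one.

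**Step 2: type I error at n = 100, one trait and one outcome.** A normal shift of spurious r x sqrt(97) gives 6.8% at 0.04 (shift 0.394) and 14.4% at 0.09 (shift 0.886). Simulation of the change-score regression (4,000 runs per row) gives:

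| Each correlation | Covariate omitted | Covariate x time included |
|---|---|---|
| 0.1 | 5.6% | 5.6% |
| 0.2 | 6.9% | 5.0% |
| 0.3 | 14.7% | 4.6% |

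The simulation error near 5% is about sqrt(0.05 x 0.95 / 4000) = 0.3 percentage points. In the first row both analyses give the same rate, so omission does no visible harm there.

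**Step 3: which term removes the bias.** GEE with exchangeable correlation, 20,000 simulated patients with both assessments, true trait x time effect zero:

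| Each correlation | No covariate | Main effect only | Main effect + covariate x time |
|---|---|---|---|
| 0.1 | 0.011 | 0.011 | 0.000 |
| 0.2 | 0.037 | 0.037 | −0.002 |
| 0.3 | 0.089 | 0.089 | 0.002 |

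(Standard error 0.007 throughout.) With both waves present, a covariate main effect shifts both time points equally and cannot touch the trait x time term. The same holds for diagnosis: entered only as a main effect, it would leave that term as it was.

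**Step 4: cost in power.** With f² = 0.243² / (1 − 0.243²) = 0.0625, reduced by the factor (1 − R²) when the covariates explain a share R² of trait variance, noncentral-F power at n = 100 for d = 0.5 is:

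- no extra terms: 0.697
- five extra terms unrelated to the trait: 0.696
- R² = 5%: 0.674
- R² = 10%: 0.651

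Any gain from covariates that explain change itself is ignored.

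**The case against.** Four arguments have weight.

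*The question is largely predictive.* The article says its interest is in covariance and disclaims strict causal conclusions. For whether baseline traits predict course, a model without demographics is legitimate. This stands, and is why the unadjusted model should be kept. It does not cover the claims about mechanisms and reduced effectiveness.

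*The covariate list may sit in a fuller protocol.* Recording a variable is no promise to adjust for it, no sentence says that diagnosis is the only covariate, and the article points to a protocol that is not shown. A reader might infer that the plan contradicts itself or expressly rules out demographics; the text supports neither. But the article does name the adjustment for its confirmatory models and claims exact prespecification, so the stated choice can be assessed.

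*Confounding is assumed, not shown.* Nothing in the article says that age, sex or education relates to symptom change in this sample. At correlations of 0.1 the effect is negligible. If the five BFI traits enter one model, the partial associations count, and the simple product does not give them. All of this stands.

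*Adjustment can do harm.* Education may partly follow from a trait such as conscientiousness, so adjusting for it could remove part of the trait effect. In the second paper, hypothesis (4) asks what the IIP and IMI-C each add to the other; putting demographics in first would change that question. Both points stand and limit the fix.

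**Conclusion.** The point holds as a weakness in the choice of covariates. The adjusted GEE models, as described, leave trait-by-time effects open to confounding by age, sex and education, although those variables are recorded.

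The size rests wholly on assumed correlations. Over 0.1 to 0.3 the bias runs from trivial to d about 0.18. That is small beside the predicted d > 0.5, but at the upper end it nearly triples the error rate of a single test. These figures are for one omitted covariate with a linear effect; several could add up or cancel.

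A reader might go further and conclude that the expected effects of neuroticism or conscientiousness are demographic artefacts, or that adjustment would make the estimates unconfounded. The article supports neither. It gives no evidence on these associations, and adjustment deals only with the variables entered, in the form entered.

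**What to change.** Before the follow-up data are analysed, prespecify for the adjusted GEE models of both papers:

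- age and sex, each with its interaction with time;
- diagnosis with its interaction with time, in a few broad groups. Study Site and Sampling Procedure lists ten problem types and also patients without a diagnosis. Eleven categories would mean about 100 / 11 = 9 patients each and ten interaction terms.

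Add education x time as a sensitivity analysis only. Keep the unadjusted model as the answer to the predictive question. Leave hypothesis (4) of the second paper as planned, and report any demographic-adjusted version of it only as a sensitivity analysis.

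No new data are needed. The price is a modest loss of precision, and it falls mainly where the covariates are related to the trait: power for d = 0.5 goes from about 0.70 to 0.67 or 0.65 if they explain 5% or 10% of trait variance. Unrelated covariates cost almost nothing. Confounding by unrecorded factors remains and should be stated as a limitation.

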**Figure 1 F1:**
[figure not shown]
**Participant flowchart**. BFI, Big Five Inventory; IIP, Inventory of Interpersonal Problems; IMI-C, Impact Message Inventory-Circumplex; GAF, Global Assessment of Functioning; BSI, Brief Symptom Inventory; INK, Incongruence Questionnaire; ICD-10, International Classification of Diseases 10th Edition.

## Stepwise Procedures

This observational naturalistic study was approved by the Cantonal Ethics Committee of Zurich (KEK) in December 2015 (reference number 2015-0601). The project is financially supported by a grant from the OPO Foundation (reference number 2016-0038) awarded in June 2016 to [name]. The funder will have no bearing on the conduct, analysis, and interpretation of the data and the decision to submit a manuscript for publication. As stated above, all German-speaking patients starting psychotherapy at KGI in September 2015 and afterward will be included in the dataset. At present a total of *n* = 58 baseline and *n* = 6 follow-up measurements have been completed (effective October 2016). To achieve the projected sample size of *n* = 100 at 6-month follow-up, data collection will presumably continue until autumn 2017. Data analysis and manuscript draft will start immediately once the projected sample size has been reached. Study results are intended to be published in leading journals of clinical psychology, psychopathology, and psychotherapy.

